### 2.8. Secondary Outcomes

Clinical trial variables are to be evaluated from the baseline (v0) to the end of the intervention (v5). The mean of the difference between these visits will be compared with those calculated in the other two treatment groups. The evolution of all clinical trial variables will also be evaluated through the different intervention visits where they will be measured (v1, v2, v3, v4, or v5).

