### 2.12. Data Collection and Management

The study data will be treated following the referenced confidentiality standards and the quality criteria described above. A specific database will be created in Microsoft Office Standard Excel 2013 (Microsoft® Company) using a standardized database creation process. All data collected in the research data collection will be entered by a member of the research team into the original database. This database will be designed with a double-entry system and filters to prevent and detect any type of inconsistency or error. Data will be incorporated based on the ID patient and visit where the results will be collected (vS, v1, v2, v3, v4, v5). The clinical trial Principal Investigator oversaw supervising the database construction. Databases will be stored in the HULP repository within the closed circuit, and RDC will be stored in the nutritionist’s office in a locked filing cabinet.

During the database creation process, a member of the research team will be in charge of notifying the principal investigator of the presence of missing values. These values will be those that for any reason have not been reflected in the RCD by the patient. The member of the research team indicated the affected cells in the database by coloring them yellow with the word “missing”. Once indicated, the sample size of the affected variable will be adjusted for subsequent statistical analysis. In no case will the patient record be deleted, only the missing value that affects the variable.

After incorporating all the data into the database, they will be duly cleaned, avoiding the appearance of symbols (<, >, etc.) that could interfere with the subsequent statistical analysis. The same member of the research team in charge of creating the original database will be in charge of creating a second database in which alphanumeric coding will be given to each variable to guarantee masking during data analysis. If so needed, new variables such as groupings or sums will be created to facilitate comparison between protocol main visits. When the database is finished, the Principal Investigator will oversee sending the Excel file to the Department of Biochemistry and Molecular Biology II (University of Granada) for analysis.

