### 2.13. Statistical Methods

A preliminary study to identify out-of-range values or outliers will be performed. Outliers will be considered those that are greater than the value of the means ± 2 standard deviations. A qualitative descriptive analysis of data will be performed in absolute and relative frequencies and percentages. Quantitative data will be presented as the means ± standard deviations (SD), medians, ranges, percentiles, and percentages. The normality of distribution for each variable will be determined using Kolmogorov–Smirnov and Shapiro–Wilk tests. Levene’s test will be used to evaluate the homogeneity of variances. Parametric or nonparametric tests will be performed depending on whether the variables are normally distributed.

A multivariate analysis of covariance (MANCOVA) for repeated measures will be used to analyze the relationship between a dependent variable and multiple independent variables while controlling for the effects of one or more covariates. A separate analysis of covariance (ANCOVA) on each independent variable controlling for the effects of the covariates will be carried out.

A general linear model (GLM) will be used to model the linear relationship between a dependent variable and one or more independent variables (including continuous, categorical, and binary data). The analysis of the qualitative variables and percentages will be carried out through chi-square (χ^2^) or Fisher’s F analysis depending on the variable sample size.

Specific statistical and bioinformatic software will be used for metabolome, microbiome, and metagenome analyses. This includes PCA, OPLS-DA, analysis of metabolic pathways with mummichog (https://shuzhao-li.github.io/mummichog.org/, accessed on 1 October 2023) and GSEA, PERMANOVA, etc., using the R Project for Statistical Computing. R (https://www.r-project.org/, accessed on 1 October 2023).

Double-sided tests will be applied when needed, and a *p*-value < 0.05 will be considered statistically significant. Data will be analyzed using IBM SPSS Statistics for Windows, version 21.0 (IBM Corp., Armonk, NY, USA) and the R Project for Statistical Computing. R is available as Free Software under the terms of the Free Software Foundation’s GNU General Public License in source code form (https://www.r-project.org/ (accessed on 1 October 2023)).

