##### Plasma Cytokines

Based on previous reports [95,96,97,98], relevant molecules previously described as associated with inflammatory processes and cancer cachexia will be selected for their analysis in plasma. Namely, TNFα, IL-6, IL-1β, IFN-γ, IL-4, IL-10, IL-15, IL-1RA, IL-15, IL-1RA, sIL-6R, sTNFRI, sIL-6R, sTNFRI, sTNFRII, human leukemia inhibitory factor (LIF), human ciliary neurotrophic factor (CNTF) and human proteolysis-inducing factor/dermicidin (PIF/DCD) will be analyzed.

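### Removing '<' and '>' from the database without a flag or a coding rule loses the censoring in secondary biomarker results and can distort their arm contrasts

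*Protocol article*

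**What the plan says.** Section 2.12 (Data Collection and Management) states the rule. Once data entry is complete, "they will be duly cleaned, avoiding the appearance of symbols (<, >, etc.) that could interfere with the subsequent statistical analysis". The same team member then builds a second file with coded variable names, and this is sent to a university department for analysis. The cleaning step mentions no substituted value, missing code, flag or reporting limit.

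Two neighbouring rules do not fill the gap. The missing-data rule in 2.12 covers values that were never recorded: "In no case will the patient record be deleted, only the missing value that affects the variable". The screen in 2.13 concerns distributional extremes: "Outliers will be considered those that are greater than the value of the means ± 2 standard deviations".

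Section 2.13 plans repeated-measures MANCOVA and ANCOVA, and "A general linear model (GLM) will be used to model the linear relationship between a dependent variable and one or more independent variables". It adds that "Parametric or nonparametric tests will be performed depending on whether the variables are normally distributed". No censored-data method is named.

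The results most plausibly affected are secondary. Under Plasma Cytokines in section 3.5.2, a panel of interleukins, TNF-alpha and soluble receptors is listed, and "human leukemia inhibitory factor (LIF), human ciliary neurotrophic factor (CNTF) and human proteolysis-inducing factor/dermicidin (PIF/DCD) will be analyzed". For secondary outcomes in general, section 2.8 says "The mean of the difference between these visits will be compared with those calculated in the other two treatment groups". That section starts the comparison at v0, but section 4.2.1 takes the first study bloods, including cytokines, at v1, and section 2.8.9 compares v1 with v5 for general biochemistry. The working baseline for blood markers is therefore v1.

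**The concern.** A result reported as '<x' has no exact value; it is known only to lie below x. The cleaning rule treats the symbol as clutter, although it is the part of the entry that says the value is censored. Once it has gone, a measured x and a censored x cannot be told apart in the analysis file.

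If the number is kept, a patient below the limit at both v1 and v5 has a change of exactly zero, and a patient who falls below the limit has the fall cut off there. Section 6 expects reductions in pro-inflammatory cytokines and tumour-derived factors, so values at the low end are where the expected effect would show. Results reported as '>x' are the mirror image. If the cell is blanked instead, the lowest values drop out of both arms selectively.

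Section 2.10 intends the pilot's results to guide the size of later efficacy studies. A distorted difference or SD would carry forward if one of these markers were used for that purpose.

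**Working it through.** **Nothing to reproduce.** The protocol gives no detection limit, censored share or biomarker SD, and section 2.10 reports no sample size calculation. The inputs below are assumptions, shown as a range.

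**Set-up.** On the log scale, control values at v5 follow N(0, 1) and treated values N(−0.5, 1), so the true difference is −0.5 SD. The reporting limit L is placed so that a share c of control values falls below it.

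**Case 1: symbol removed, limit kept.** The mean of the cleaned values in an arm with true mean μ is

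E(μ) = Φ(L−μ)·L + μ·[1 − Φ(L−μ)] + φ(L−μ).

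For c = 10%, L = −1.2816:
- Control: 0.10 × (−1.2816) + 0.1755 = 0.047.
- Treated: 0.2172 × (−1.2816) − 0.5 × 0.7828 + 0.2939 = −0.376.
- Difference: −0.376 − 0.047 = −0.423, which is 0.846 of the true −0.5, or 15% attenuation.

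**Case 2: cell blanked.** The arm mean is μ + φ(L−μ)/[1 − Φ(L−μ)].

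| Control values censored | Limit kept: estimate (SD) | Attenuation | Cell blanked: estimate (SD) | Attenuation |
|---|---|---|---|---|
| 2% | −0.481 | 4% | −0.422 | 16% |
| 5% | −0.458 | 8% | −0.372 | 26% |
| 10% | −0.423 | 15% | −0.319 | 36% |
| 20% | −0.360 | 28% | −0.256 | 49% |
| 40% | −0.251 | 50% | −0.183 | 63% |

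**Change scores.** With comparable v1 distributions, the cleaned v1 mean has the same expectation in both arms and cancels. With the limit kept, the expected difference in v1-to-v5 change therefore equals the v5 difference above.

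**Case 3: half the limit substituted.** Halving moves each censored value down by a further ln 2 / σ, where σ is the log-scale SD. The ratio of estimate to truth becomes the limit-kept ratio plus (ln 2 / σ) × (treated share censored − control share censored) / 0.5.
- c = 10%, σ = 0.5: 0.846 + 1.386 × (0.2172 − 0.10)/0.5 = 1.17, an inflation.
- c = 30%, σ = 0.5: 0.607 + 1.386 × (0.4903 − 0.30)/0.5 = 1.13, an inflation.
- c = 30%, σ = 1: 0.607 + 0.693 × (0.4903 − 0.30)/0.5 = 0.87, an attenuation.

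**Case 4: baseline imbalance, limit kept.** Let both arms truly fall by 0.5 SD, one from a v1 mean of 0 (30% below the limit) and the other from 0.5.
- Higher-baseline arm: 0.190 − 0.580 = −0.389 (from unrounded means).
- Lower-baseline arm: −0.113 − 0.190 = −0.304 (likewise).
- Spurious difference in change: −0.389 − (−0.304), about −0.09 SD, where the truth is zero.

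**Raw scale.** If a lognormal marker is analysed without a log transform, the limit-kept loss is smaller. With log-SD 1, simulation gives ratios of 0.98, 0.90 and 0.78 at 10%, 30% and 50% censored.

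**Tests.** With the limit kept and comparable arms, simulated t-tests at 10 and at 7 patients per arm keep Type I error at or below about 0.05. Power for a 1 SD difference at 10 per arm falls from 0.56 without censoring to 0.43 at 30% and 0.30 at 50%.

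**The case against.** The strongest reply is that the sentence is loose rather than wrong. It does not tie the symbols to assay limits, and it does not say that '<x' becomes 'x'. Half-limit substitution, a missing code or a separate coded variable would also satisfy it. The full assay methods are in File S3, and coding of results below quantification is often left to a laboratory manual or analysis plan, neither of which is shown. This stands in part. The link to reporting limits is an inference, though a strong one, and the replacement value is unknown. But the article does more than stay silent: it orders the symbols removed and provides nothing to keep their meaning.

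A second reply is that section 2.13 already allows nonparametric tests, and that ties at a limit make rejection of normality more likely. This helps in some cases, but the choice rests on a normality test in a very small sample (section 5 reports 21 completers), and blanked cells would not be recovered.

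A reader might also infer that the loss is permanent. The documents do not support that. Section 2.12 keeps the data collection forms in a locked cabinet, section 2.2 archives the paper records, and the department that runs the specialised assays (section 3.5.2) is also the one that receives the file for analysis. What lacks the mark is the analysis file as described.

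**Conclusion.** The point holds as a low-severity fault in a stated data-handling rule. Results beyond a reporting limit would enter the section 2.13 models as exact numbers or be lost, depending on a choice the protocol does not fix.

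A reader might conclude that arm differences are always biased toward zero. That goes too far. Attenuation is the expected result if the limit is kept with comparable baselines, or if the cell is blanked. Half-limit substitution can inflate the difference, and baseline imbalance can create one.

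The size depends on the censored share, which is not given. On the log scale, with a 0.5 SD true difference and the limit kept, the loss is minor at 2% to 5% censored (4% to 8%), and reaches 28% at 20% and 50% at 40%. The higher shares are illustrative; nothing in the document shows that any marker reaches them.

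Only secondary biomarkers in an exploratory pilot planned for 30 patients are concerned. The primary outcome is an electrogustometry threshold in dB and is untouched.

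**What to change.** In section 2.12, replace the removal of symbols with this rule: store the numeric limit and add a flag (below range, in range, above range) for each affected variable, and carry the flag into the coded file sent for analysis.

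In section 2.13, add that for any marker with flagged values the arms are compared with a rank-based test or a censored (Tobit) model adjusted for the v1 value. Where most values are below the limit, compare the proportion detected. Report the percentage outside range by arm and visit.

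The cost is one extra column per affected variable and a different test for some markers. The small downside is that rank-based results are less direct to read than mean changes. If File S3 or an analysis plan already holds such a rule, a cross-reference and a corrected sentence in 2.12 would be enough.

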### 2.13. Statistical Methods

A preliminary study to identify out-of-range values or outliers will be performed. Outliers will be considered those that are greater than the value of the means ± 2 standard deviations. A qualitative descriptive analysis of data will be performed in absolute and relative frequencies and percentages. Quantitative data will be presented as the means ± standard deviations (SD), medians, ranges, percentiles, and percentages. The normality of distribution for each variable will be determined using Kolmogorov–Smirnov and Shapiro–Wilk tests. Levene’s test will be used to evaluate the homogeneity of variances. Parametric or nonparametric tests will be performed depending on whether the variables are normally distributed.

A multivariate analysis of covariance (MANCOVA) for repeated measures will be used to analyze the relationship between a dependent variable and multiple independent variables while controlling for the effects of one or more covariates. A separate analysis of covariance (ANCOVA) on each independent variable controlling for the effects of the covariates will be carried out.

A general linear model (GLM) will be used to model the linear relationship between a dependent variable and one or more independent variables (including continuous, categorical, and binary data). The analysis of the qualitative variables and percentages will be carried out through chi-square (χ^2^) or Fisher’s F analysis depending on the variable sample size.

Specific statistical and bioinformatic software will be used for metabolome, microbiome, and metagenome analyses. This includes PCA, OPLS-DA, analysis of metabolic pathways with mummichog (https://shuzhao-li.github.io/mummichog.org/, accessed on 1 October 2023) and GSEA, PERMANOVA, etc., using the R Project for Statistical Computing. R (https://www.r-project.org/, accessed on 1 October 2023).

Double-sided tests will be applied when needed, and a *p*-value < 0.05 will be considered statistically significant. Data will be analyzed using IBM SPSS Statistics for Windows, version 21.0 (IBM Corp., Armonk, NY, USA) and the R Project for Statistical Computing. R is available as Free Software under the terms of the Free Software Foundation’s GNU General Public License in source code form (https://www.r-project.org/ (accessed on 1 October 2023)).

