#### 2.8.1. Chemical Taste Perception

Chemical taste perception is evaluated by the taste strips test. Taste sensitivity evaluation is necessary for a proper diagnosis and subsequent treatment of taste disorders [30]. Through the taste strips test, it is possible to obtain a total score and identify those patients with taste alterations such as parageusia (incorrect taste identification) and hypogeusia or ageusia (decreased taste sensitivity or lack of taste, respectively) from those with normogeusia (normal perception of taste). Once patients have been diagnosed, the changes that have arisen from the beginning to the end of the intervention and the differences observed with the different treatment groups are to be evaluated.

The taste disturbance prevalence ranges from approximately 20 to 86% [31], which occurs approximately 2–3 weeks after the start of cancer therapy and persists throughout the treatment [32]. These distortions often contribute to difficulties maintaining food intake during treatment [33], thus increasing the risk of malnutrition [28]. As chemical test perception is complementary to electrical taste perception, the consumption of the miraculin-based food supplement might enhance food intake and improve nutrition status due to better food taste perception.

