#### 2.8.3. Nutritional Status

Malnutrition is the state resulting from a lack of intake or uptake of nutrition that leads to changes in body composition, reduced fat-free mass and body cell mass, decreased functional capacity, and impaired clinical outcome from disease [40]. This can result from starvation, disease, or aging combined or as separate entities [41]. However, when malnutrition is caused by a concomitant disease, it is referred to as disease-related malnutrition (DRM), where inflammation is usually present [42].

Malnutrition is a condition that is highly prevalent in cancer patients. It is estimated that up to 10–20% of cancer patients die due to malnutrition rather than the tumor [43]. This appears as a consequence of both the tumor and the antineoplastic treatments and negatively affects the quality of life and the effectiveness of treatments. Thus, the assessment of nutritional status in cancer patients is crucial to improve disease prognosis.

Nutritional status is evaluated by the GLIM criteria at the beginning and the end of the intervention (3 months), a period where it is possible to assess the nutritional intervention effect. From the assessment of the nutritional status, a diagnosis of the type of malnutrition presented (moderate or severe) is obtained. Additionally, the nutritional status of the patients will be evaluated at visits 3 and 4 to evaluate the evolution of the patient throughout the clinical trial. For the rest of the variables, the average change occurring from the beginning to the end of the intervention between the different treatments is evaluated.

According to the practical guidelines for clinical nutrition in cancer, nutritional intervention has to lead to increasing oral intake in cancer patients who are malnourished or at risk of malnutrition [43]. In addition to dietary advice, the nutritional intervention is intended to treat symptoms and derangements impairing food intake (e.g., dysgeusia) and offering oral nutritional supplements (ONS) when necessary. In this regard, it is possible that improvement in taste distortions has a positive effect on food intake and, therefore, on the nutritional status of cancer patients.

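### Chi-square/Fisher for GLIM grade is valid between arms, but it discards the order of the grades and, on the end visit alone, the baseline grade

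*Protocol article*

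**What the plan says.** Section 2.13 names one approach for categorical data: "The analysis of the qualitative variables and percentages will be carried out through chi-square" or Fisher, depending on sample size. No paired, clustered or ordinal method is named there. The other methods in 2.13 are not tied to a categorical outcome:

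- The general linear model describes a linear relationship with "one or more independent variables (including continuous, categorical, and binary data", so the categorical and binary data it mentions are predictors.
- The remaining rule turns on normality: "Parametric or nonparametric tests will be performed depending on whether the variables are normally distributed". It names no test and does not mention grades.

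Section 2.8.3 takes GLIM status at the beginning and at three months, yielding moderate or severe malnutrition. It adds that "the nutritional status of the patients will be evaluated at visits 3 and 4 to evaluate the evolution of the patient". It keeps average change for the other variables, which leaves the GLIM grade with the chi-square/Fisher sentence.

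The general contrast for secondary outcomes in 2.8 is between arms: "The mean of the difference between these visits will be compared with those calculated in the other two treatment groups". Section 2.8.1 likewise asks for "the changes that have arisen from the beginning to the end of the intervention and the differences observed with the different treatment groups". Section 2.12 lets derived variables, such as groupings, be created to compare visits. The significance level is 0.05.

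**The concern.** GLIM grade is how the trial measures the nutritional status named in its title. It has three features that matter for the choice of test. It is ordered (none, moderate, severe at follow-up). It has a baseline value in every patient, because malnutrition is an entry criterion. It is repeated on the same patient up to four times.

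Pearson chi-square and Fisher use none of these. They treat severe-to-moderate as no different in kind from severe-to-none, and they have no place for a baseline covariate. With 10 patients per arm there is little information to spare. Section 6 expects the trial to show whether nutritional status improves and at which dosage, and 2.10 uses the results to size later studies.

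The repeated gradings raise a second question: how the evolution over v3, v4 and v5 is to be analysed when the only named categorical test needs one independent record per patient.

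**Working it through.** **1. How the document uses the test.** Table 3 shows categorical p-values. The sex percentages of 62.5, 33.3 and 85.7 fit 5/8, 2/6 and 6/7 women, that is 13 of 21 (61.9%, as section 5 states). Expected women are 8×13/21 = 4.952, 6×13/21 = 3.714 and 7×13/21 = 4.333. Expected men are 3.048, 2.286 and 2.667. Pearson X² = Σ(O−E)²/E = 0.001 + 2.077 + 1.683 = 3.761 on 2 df, so p = exp(−3.761/2) = 0.1525; the table gives 0.153. Cancer type gives X² = 14.65 on 20 df, p = 0.796, as printed. Both are between-arm tests with one record per patient.

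**2. Inputs the documents do not give.** They state no within-patient correlation, grade split or effect size for GLIM. Assumed here: a latent normal score per patient and visit, cut into grades; every patient moderate or severe at baseline; three grades possible at follow-up in the power runs. Correlations are shown as a range. Type I error in steps 3 and 4 uses a 50/50 moderate/severe split, except where marked.

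**3. Type I error of between-arm use (nominal 5%).** Columns are latent correlation.

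| Chi-square across arms | 0.3 | 0.5 | 0.7 | 0.9 |
|---|---|---|---|---|
| End-visit grade, N = 30 | 4.0% | 4.4% | 4.2% | 4.1% |
| Per-patient change category, N = 30 | 4.5% | 4.1% | 3.4% | 1.9% |

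With 21 patients (8/6/7) the end-visit test gives 5.2% to 5.6% and the change-category test 3.9% to 1.1%. Neither is inflated.

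**4. What would go wrong across or over visits.** The plan prescribes neither of these uses.

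| Use, N = 30 | 0.3 | 0.5 | 0.7 | 0.9 |
|---|---|---|---|---|
| Baseline against end, as if different patients | 3.2% | 1.5% | 0.5% | 0.1% |
| Four visits pooled, across arms | 16% | 24% | 32% | 41% |

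Pooling only the three follow-up visits gives 12%, 17% and 25% at correlations of 0.3, 0.5 and 0.8.

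**5. Power of between-arm use.** Three arms of 10, 1 SD latent shift in both active arms. The ordinal comparator is the Cochran-Mantel-Haenszel row-mean-score test stratified by baseline grade. For each active arm k, U_k is the sum over strata of (total grade score in arm k − n_k × stratum mean). V is the sum over strata of s²(diag(n) − nn′/N_s), where s² is the stratum variance of the scores and N_s the stratum size. The statistic is U′V⁻¹U on 2 df.

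| Test | 0.3 | 0.5 | 0.8 |
|---|---|---|---|
| Chi-square, end-visit grade | 37–38% | 37–38% | 37–38% |
| Chi-square, change category | 31% | 36% | 56% |
| Row-mean-score, stratified by baseline | 51% | 53% | 67% |

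Type I error of the ordinal test is near 5%. With 8/6/7 completers, end-visit chi-square has about 25% power against 33% to 46% for the ordinal test.

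**6. A smaller effect.** With a half SD shift at the lower dose and 1 SD at the higher (10 per arm, correlation 0.5 and 0.8), the powers are:

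- end-visit chi-square: 28% and 28%
- change-category chi-square: 20% and 31%
- Kruskal-Wallis on the end grade (order only): 36% and 38%
- Kruskal-Wallis on change (order and baseline): 38% and 54%

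**The case against.** A reader might infer that the plan's test has the wrong error rate because it treats repeated gradings of one patient as independent. The documents do not support that. No section says that visits will be cross-tabulated or pooled. Section 2.8 sets its contrast between arms, 2.8.8 compares percentage change between treatments, and Table 3 reproduces as one record per patient. The rates in step 4 therefore belong to analyses that the plan does not prescribe.

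Nor must the named test discard baseline. Section 2.12 permits derived groupings, and chi-square on improved/same/worse is valid and uses the baseline grade. At correlation 0.8 it has more power than the end-visit test (56% against 37–38%). What it still loses is order.

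The scope is also narrower than all categorical outcomes. Taste strips, smell and grip strength have quantitative scores, and for grip the plan explicitly compares mean change. The point mainly concerns GLIM grade.

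Finally, this is a journal article, a SAP may exist, and 2.13 mentions unnamed nonparametric tests. That lowers the weight of the point but does not remove it. Section 2.13 states a method for all qualitative variables, and that method fits a repeated ordered grade poorly.

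**Conclusion.** The point holds as a matter of efficiency and of fit between test and outcome. Between arms, chi-square/Fisher on GLIM grade is valid but wastes grade order and, at the end visit alone, baseline. Under the stated assumptions the cost is about 37% power against 51–67% with 10 per arm, or about 25% against 33–46% with 8/6/7 completers. The correlations, grade split and 1 SD shift are assumptions. A smaller effect leaves every version underpowered, with the same advantage for order and baseline combined.

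For evolution over visits, 2.13 names no suitable method. The risk of a wrong error rate arises only if someone tabulates or pools visits, which the plan does not ask for; the wording should rule it out.

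Severity is minor. GLIM grade is a secondary outcome in an exploratory pilot, and the primary electrogustometry comparison, made between arms on per-patient differences, is unaffected.

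**What to change.** In 2.13, limit chi-square/Fisher to variables recorded once, such as sex and cancer type, and add for GLIM grade:

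- **Main comparison:** arms compared on the v5 grade with a Cochran-Mantel-Haenszel row-mean-score test stratified by baseline grade, with a permutation p-value. Proportional-odds regression adjusted for baseline grade may support it.
- **Evolution over v3, v4 and v5:** a method clustered on patient, or the same stratified between-arm test at each visit. State that gradings from several visits are not tabulated or pooled as independent records.

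The cost is one paragraph and slightly more analysis work, with no new data, visits or patients. Ordinal regression can be unstable at about 10 per arm, which is why the permutation test should be the default and the model only supportive. If a SAP already specifies such an analysis, aligning the sentence in 2.13 with it is enough.
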